#### 5.5.4 Process evaluation

We will follow the MRC guidance on process evaluation [Moore], which describes three components using a mixed-methods approach: implementation or delivery; mechanisms of impact; contextual factors. Process evaluation of complex interventions usually requires a combination of quantitative and qualitative methods: at the feasibility and piloting stage, basic quantitative measures of implementation may be combined with in-depth qualitative data to provide detailed understandings of intervention functioning on a small scale [Moore 2014] (Figure).

Quantitative measures will include structured observations of audio recorded ACP conversations. These will be used to examine aspects of fidelity (such as consistency with SDM principles), and dose (the duration of conversations).

Qualitative methods will be used to investigate mechanisms of impact and contextual factors, using NPT [Murray 2010, May 2018]. NPT identifies four essential determinants of ‘normalising’ complex interventions into common practice: *coherence* (the extent to which an intervention is understood as being meaningful, achievable and valuable); *cognitive participation* (the engagement of HPs necessary to deliver the intervention); *collective action* (the work that brings the intervention into use); and *reflexive monitoring* (the on-going process of adjusting the intervention to keep it in place) [May 2018]. These components are considered to be dynamic and interact within the wider context of the intervention, such as existing organizational structures and procedures [May 2018].

## 6 EXPECTED RESULTS AND IMPACT

*Research* – The safety and efficacy of the [ConCure-SM](#) intervention will be preliminary assessed, using mixed methods approach. A protocol for a phase III trial will be developed if this trial's findings demonstrate that: a) the intervention is acceptable to > 70% of participants (pwPMS, SOs, and physicians); > 50% of eligible pwPMS are recruited; > 70% of recruited pwMS are retained; > 25% of recruited pwMS complete an ACP document.

*Deliverables* - This study will produce an HP training program and booklet that are specific for ACP in pwPMS, devised with the contribution of the key stakeholders. The electronic format will ease the incorporation of the ACP document (and its updates) in the electronic medical record, that is currently available in some Italian regions and hopefully will be soon available all over Italy.

*Use in other conditions* – The [ConCure-SM](#) intervention can be adapted for use in other neurological and non-neurological conditions for which consolidated ACP interventions are not available.

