### 3. AIMS

The present study describes the second phase of the *ConCure-SM* project. The objectives of this pilot and feasibility study are as follows:

1. To determine how many people accept the invitation to participate in the study.
2. To determine how many participants receive the intervention.
3. To estimate recruitment and refusal rates, and 6-month follow-up rates.
4. To estimate ACP completion during the 6-month follow-up (primary study outcome).
5. To estimate occurrence of serious adverse events (SAEs) and adverse events (AEs) during the 6-month follow-up.
6. To assess, qualitatively, the acceptability of the recruitment processes, assessments, intervention delivery and secondary outcome measures with key stakeholders.
7. To measure changes in secondary outcome measures.
8. To explore the barriers and facilitators to implementing ACP in pwPMS, and the influence of the clinical setting.
9. To inform the sample size estimation for a subsequent RCT, should this be feasible.

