## **5.4 Nested qualitative study**

Our referral framework was the mixed methods approach which, by integrating the quantitative findings with the qualitative findings, aims to provide a more comprehensive picture of the intervention than either method can do [Craig 2008]. Quantitative and qualitative data will be collected in parallel and then analyzed and integrated using Normalization Process Theory (NPT). We will perform semi-structured one-on-one interviews with pwPMS and SOs chosen using a maximum variation strategy, and FGMs of physicians involved in intervention delivery and other HPs from the center (Figure). For the pwPMS and the SOs the personal semi-structured interviews were considered most appropriate to limit interview burden and hopefully make it easier for participants to express their feelings, and recount their experiences of the intervention. For the patient referring physicians and the other HPs we chose the FGMs as they promote interaction and exchange of ideas. A minimum of 10 interviews (five with pwPMS and five with SOs) and two FGMs will be held, the final number depending on the achievement of 'data saturation' [Denzin 2000]. We will use NPT to determine if, and in what ways, the *ConCure-SM* intervention can be successfully 'normalized' (embedded) into clinical practice. Further, we will use qualitative data to identify required modifications and to develop practical strategies for enabling and sustaining the *ConCure-SM* intervention delivery in clinical settings.

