### 5.5.2 Statistics

Descriptive statistics will be calculated for general and clinical variables. Specifically, continuous variables will be summarized by their mean and SD, or median and interquartile range; categorical variables will be summarized as numbers and percentages.

Categorical variables will be compared using the chi-squared test. The normality assumption of continuous variables will be tested with the Shapiro-Wilk test. Depending on data distribution, between-group comparisons will be carried out using either the two-sided unpaired t-test or the Wilcoxon two sided two sample test; within-group comparisons will be carried out using either the paired t-test or the Wilcoxon signed-rank test; correlations will be computed using Pearson's or Spearman's coefficients.

Our primary end-point is the proportion of pwPMS completing an ACP during the six-month period. Change in the secondary outcome measures will be also calculated. In addition, we will calculate the following feasibility outcomes:

- Recruitment rate (enrollment per month; reasons for non-eligibility, non-enrollment).
- Retention rate (proportion completing the intervention and study follow-up).
- Missing data (proportion fully completed, for each scale, at each time point).

Data will be analyzed according to the intention-to-treat principle. Multiple imputation of missing values will employ Rubin's approach. A p-value less than 0.05 will be considered statistically significant. No correction for multiple comparisons will be applied. All analyses will be performed using STATA 16 (College Station, Texas 77845 USA). Assumptions in determining the sample size of the main trial will be checked.

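### One of the four progression criteria, acceptability to more than 70% of patients, significant others and physicians, has no planned measure and conflicts with the aim of assessing acceptability qualitatively

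*Protocol*

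**What the plan says.** Protocol section 6 lists four findings that would lead to a phase III protocol:

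- acceptability: "the intervention is acceptable to > 70% of participants (pwPMS, SOs, and physicians");
- recruitment: "> 50% of eligible pwPMS are recruited";
- retention: "> 70% of recruited pwMS are retained";
- completion: "> 25% of recruited pwMS complete an ACP document".

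Section 3, objective 6, sets the method for acceptability: "To assess, qualitatively, the acceptability of the recruitment processes, assessments, intervention delivery and secondary outcome measures with key stakeholders". Section 5.4 gives the size of the qualitative work: "A minimum of 10 interviews (five with pwPMS and five with SOs) and two FGMs will be held". The final number depends on data saturation. Interviewees are chosen for maximum variation (section 5.4.1), and each focus group mixes 6 to 10 physicians and other professionals (section 5.4.2).

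Section 5.5.2 lists the feasibility outcomes to be calculated: "Recruitment rate (enrollment per month; reasons for non-eligibility, non-enrollment"), "Retention rate (proportion completing the intervention and study follow-up"), and the proportion of complete data for each scale. Acceptability is not among them.

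**The concern.** A threshold of more than 70% is a statement about a proportion. It needs a yes or no for each person, a denominator and, with three kinds of respondent, a rule for combining them. The protocol supplies none of these for acceptability, and the method it does state is not designed to produce a proportion. The protocol's summary says the study will inform the decision to proceed to a randomized trial. If the gap stays, this criterion would have to be judged by a reading that the protocol does not fix, possibly after the results are known. Once the T1 assessments are over, a rating given soon after the conversation can no longer be collected.

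**Working it through.** The protocol gives no figure for this criterion that could be reproduced. The sample size in section 5.5.1 concerns completion of an advance care plan only. The check is therefore a comparison of each criterion with the data collected, followed by an illustration of scale.

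**1. Criteria against data**

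| Criterion (section 6) | Data behind it | Computable as planned? |
|---|---|---|
| Acceptable to >70% | No individual rating; qualitative assessment (section 3, objective 6) | No |
| >50% of eligible recruited | Counts approached, screened and eligible (section 5.2.4) | Yes |
| >70% retained | Retention rate (section 5.5.2) | Yes |
| >25% complete a document | Occurrence and signature date (section 5.3.1) | Yes |

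**2. Could a scheduled instrument serve?** Table 2 gives the construct of each scale:

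- 4-item ACP-E: engagement
- eCPS: role preference
- HADS: mood
- MSQOL-29: quality of life
- ZBI: caregiver burden
- OPTION: the physician's shared decision-making skills, scored by an observer
- QOC, QOC-SO and QOC-Doc: communication quality

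None is labelled acceptability, and no section assigns any of them to this criterion. The quantitative process measures in section 5.5.4 cover fidelity and dose.

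**3. Could the qualitative study serve?** Interviewees are picked for variety of characteristics and outcomes, and early interviews steer the choice of later ones. That suits a search for themes but does not give a representative proportion. For physicians, the source is two mixed focus groups analyzed thematically, with no individual rating planned.

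**4. Scale.** The denominators below are assumptions, because the protocol states none. For each n, the smallest count above 70% is the smallest whole x with x/n > 0.70. The exact (Clopper-Pearson) 95% limits are the 2.5% point of Beta(x, n−x+1) and the 97.5% point of Beta(x+1, n−x). When x = n, the lower limit is 0.025^(1/n) and the upper limit is 1.

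| Assumed respondents | n | Smallest pass | Exact 95% CI | Smallest count with lower limit >70% |
|---|---|---|---|---|
| Minimum patient interviews | 5 | 4/5 = 80% | 28% to 99% | none; 5/5 gives 0.025^(1/5) = 48% |
| Minimum interviews, patients and significant others | 10 | 8/10 = 80% | 44% to 97% | none; 10/10 gives 0.025^(1/10) = 69% |
| All 40 planned patients | 40 | 29/40 = 72.5% | 56% to 85% | 34/40 |
| Physicians, one per center | 6 | 5/6 = 83% | 36% to 99.6% | none; 6/6 gives 0.025^(1/6) = 54% |
| Physicians, three per center | 18 | 13/18 = 72% | 47% to 90% | 17/18 |

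The physician range follows from section 5.1.1: six centers with one to three trained physicians each, so 6 × 1 = 6 to 6 × 3 = 18.

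**The case against.** The strongest reply is that the protocol already schedules individual ratings of the conversation at T1 from exactly the three groups named: QOC for patients, QOC-SO for significant others and QOC-Doc for physicians, with items rated 0 to 10. A cut-off on one of these could be set in a statistical analysis plan, which is not at hand. That stands as a possibility, and it means a percentage for physicians is not impossible to compute. It does not close the gap. The protocol calls these forms measures of communication quality and does not name them for this criterion, and good communication is not the same as an acceptable intervention. An analysis plan also cannot analyze an acceptability rating that nobody collects.

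It is also fair that this is a pilot with point-estimate thresholds, that the criterion sits in the section on expected results, and that it does not touch the primary endpoint or its analysis. That bears on severity and stands.

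Two stronger readings are tempting:

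- A reader might infer that the whole progression rule cannot be evaluated. The documents do not support this: three of the four criteria have data behind them, and failing any one of them would be visible.
- A reader might infer that the 70% will be taken from five patients and five significant others. The protocol never says so, and those numbers are minimums. The intervals for n = 5 and n = 10 show only what such a use would be worth.

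**Conclusion.** The concern holds for one criterion of four. Acceptability to more than 70% has no planned individual-level measure, no definition, no denominator and no stated grouping, and it conflicts with objective 6. The protocol states no explicit conjunction between the four criteria; I read them as jointly required. On that reading, the study can return a no-go but cannot show that all four conditions are met. This is a gap in data collection, not just a detail left to an analysis plan. It should be fixed, but it does not threaten the primary analysis.

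**What to change.** Choose one of two routes.

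**Measure it.**

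- Add one overall-acceptability item to the T1 assessment of all patients and significant others, for example a 5-point rating with the top two categories fixed in advance as acceptable.
- Ask each delivering physician once, for example at the end of follow-up. A form filled in after every conversation would give a proportion of conversations, not of physicians.
- State whether more than 70% applies to each group or to all pooled.
- Fix the denominator in advance, including how participants with no T1 rating are counted. T1 follows the conversation, so people who never have one would otherwise drop out of the figure. One option is to count them as not acceptable, with a responders-only sensitivity analysis.
- Report exact intervals descriptively, noting that the physician group (about 6 to 18) will be imprecise.

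**Or drop the percentage**, and state the criterion as a qualitative judgement consistent with objective 6.

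The first route costs one extra question per respondent and a small amendment. It fits contacts that already exist for patients and significant others, who are telephoned at T1 for the QOC and QOC-SO. The second costs only a change of wording, but gives up a numeric threshold for this criterion.

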## 7 MEASURES TAKEN TO MINIMIZE BIAS

*Co-production* - A strong relationship exists between the engagement of stakeholders in the planning and design of a study and the subsequent quality and outcomes [Washington 2011]. The [ConCure-SM](#) resource was constructed involving the authors of the original booklet, and all the key stakeholders, in a co-production approach. The TSC is formed by the same clinicians, researchers, patient representative, and patient expert. This in order to assure all the necessary expertise to resource's development, and testing.

*Safety and quality assurance* - The study follows the CONSORT guidance for trials on social and psychological interventions (CONSORT-SPI 2018) [Grant 2018], as many of the guidance items (excluding items that are specific to the randomization nature of the study) are relevant for reporting other types of pilot and feasibility studies [Lancaster 2019]. This includes the devise of the study protocol following the SPIRIT guidance [Calvert 2018], protocol's publication, and the trial public registration (ISRCTN registry).

The consolidated criteria for reporting qualitative research will guide the presentation of findings in the study reports and publications [Tong 2007, O'Brien 2014].

All study personnel will be trained to conform to GCP regulation.

Electronic version of the study questionnaires/inventories will be used to ensure the high quality of the entered data.

Finally, an independent DSMC will monitor and supervise the progress of the study, and the safety data.

*Intervention focus* – The *ConCure-SM* intervention specifically trains MS neurologists and other HPs in ACP. We considered to target pwPMS instead, or both parties, however at this stage of the project we preferred to have a clear focus on enhancing HP competencies. A multiple-component approach that targets clinicians and pwPMS simultaneously has been suggested in other disciplines [Schichtel 2019], and will be considered in the next project phase.

*Generalizability* - Participants (pwPMS, SOs, and HPs) will be enrolled from university hospitals, research hospitals and clinical centers from the different areas of Italy. Personal, semi-structured interviews and FGMs will be run via video teleconference, which will ease participation of pwPMS with severe disability and SOs with caregiving commitments, as well as HPs. In the event potentially revealing pwPMS and/or SOs have no access to internet using personal computer or other devices, such participants will be interviewed on the telephone. The training program will be face-to-face as a substantial part of it is experiential, via role play exercises. The investigators meetings, and the meetings of the study committees will be held via teleconferences.

### 8.2 Data Safety and Monitoring Committee (DSMC)

The independent DSMC has been established to: (1) oversee the progress of the pilot study and the safety data, and ensure that it is conducted, recorded, and reported in accordance with the protocol, GCP, and the applicable regulatory requirement(s); (2) monitor and supervise the progress of the pilot study, and the safety data. Members are: [name], [name], [name], [name], and [name] (Chair). The DSMC is scheduled to meet (teleconference) before enrollment starts, at the end of the enrollment, and at the end of the follow-up, and depending on the needs of the trial. One week prior to each teleconference, the trial PI will send each DSMC member a report with trial data (overall and by site) such as recruitment rates, reasons for exclusion, reason for drop out, plus other information if needed. The DSMC should report in writing to the TSC, usually within 3 weeks after the teleconference.

### 8.3 Data Management and Analysis Committee (DMAC)

The DMAC is responsible for data entry, quality assurance, and the statistical analyses. Members are [name] (data manager) and [name]. DMAC will be in charge of the data protection to respond to the European and Italian law on privacy and data storage and conservation.

### 8.4 Qualitative Analysis Panel (QAP)

The QAP devised the design, procedures and analysis plan of the qualitative study. QAP members will conduct the personal interviews and the FGMs, and the analysis. Members are: [name], [name], [name], [name], [name], and [name].

### **8.5 HP Training Panel (HTP)**

The HTP devised the HP training program. HTP members will have responsibility of conducting the residential program, and revise it based on training findings. Members are: [name], [name], [name], [name], [name], [name], and [name].

### **8.6 Linguistic validation Panel (LP)**

The LP was appointed to translate and adapt the outcome measures not available in Italian. Members are [name], [name], [name], [name], [name] and three independent translators (section 5.3.8).

## 9 GANTT Chart

The study will be completed in two years. Each activity is reported (and detailed) in the chart below.

[figure not shown]

## **10 ETHICS AND ADMINISTRATIVE CONSIDERATIONS**

### **10.1 Ethical Considerations**

This clinical study was designed and shall be implemented and reported in accordance with the International Council for Harmonisation of Technical Requirements for Pharmaceuticals for Human Use (ICH) Guidelines for GCP, with applicable local regulations, and with the ethical principles laid down in the Declaration of Helsinki.

### **10.2 Ethics Committee Approval**

The protocol, Subject Information Sheet, Informed Consent Form must be reviewed and approved by an appropriately constituted Ethics Committee (EC), as required in chapter 3 of the ICH E6 Guideline. Written EC approval must be obtained by the Sponsor prior to shipment of study agent or subject enrolment.

### **10.3 Subject Information and Informed Consent**

Eligible subjects may only be included in the study after providing written (witnessed, where required by law or regulation), EC-approved informed consent, or, if incapable of doing so, after such consent has been provided by a legally acceptable representative of the subject. In cases where the subject's representative gives consent, the subject should be informed about the study to the extent possible given his/her understanding. If the subject is capable of doing so, he/she should indicate assent by personally signing and dating the written informed consent document or a separate assent form. Informed consent must be obtained before conducting any study-specific procedures (i.e. all of the procedures described in the protocol). The process of obtaining informed consent should be documented in the subject source documents. No study procedure can be performed before the written informed consent has been provided.

### **10.4 Confidentiality**

The investigator must ensure participant anonymity. On database and other documents, participants must not be identified by name but by patient number and initials. The investigator must keep a separate log of participants' codes, names and addresses, and signed informed consent forms, all of which must be kept strictly confidential.

Patient medical information obtained by this study is confidential and may only be disclosed to third parties as permitted by the Informed Consent Form (or separate authorization for use and disclosure of personal health information) signed by the patient, unless permitted or required by law. Medical information may be given to a pwPMS personal physician or other appropriate medical personnel responsible for the pwPMS welfare, for treatment purposes. Data generated by this study must be available for inspection upon request by representatives of the national and local health authorities, monitors, representatives, and collaborators, and the EC for each study site, as appropriate.

### **10.5 Protocol Amendments**

Any protocol amendments will be prepared by the PI. Protocol amendments will be submitted to the EC and to regulatory authorities in accordance with local regulatory requirements. Approval must be obtained from the EC and regulatory authorities (as locally required) before implementation of any changes, except for changes necessary to eliminate an immediate hazard to patients or changes that involve logistical or administrative aspects only (e.g. change in monitor or contact information).

## **11 STUDY MANAGEMENT AND MONITORING**

### **11.1 Source documents**

Source Documents are defined as original documents, data and records. These may include hospital records, medical records / outpatient data, data recorded from automated instruments, etc. Investigators should conserve all the source documents as required in the study protocol for at least two years after the end of the study.

